## **5.2 Secondary endpoints**

### **5.2.1 Secondary efficacy (clinical assessments proposed for any subsequent phase III study)**

1. Baseline demographic and clinical predictors of responders.
2. Change in body weight and BMI at every visit and assessment of historical stable weight at baseline.
3. Change in lean body mass measured at baseline and week 12 (or 24) by dual x-ray absorptiometry (DEXA) and Bioelectrical Impedance Analysis (BIA).
4. Change in muscle mass at thoracic (T4) level, measured by electronically stored data from computed tomography (CT) scans whenever they are done clinically.
5. Functional status using clinician-rated Australia-modified Karnofsky Performance Scale (AKPS) measured as area under the curve from data collected at every scheduled visit.
6. Timed *up and go test* (TUG) measured at every scheduled visit.
7. Functional performance as measured by a pedometer app (stepapp) or a wearable digital pedometer, for participants who do not have mobiles, worn for two days (preferably one weekday and one weekend day) prior to visits.
8. Nutritional intake measured by self-reported 3-day food diary, including 2 weekdays and one weekend day prior to visits. If participants do not complete the 3-day food diary prior to visits, a 24-h diet recall will be collected by the study nurse at the time of visit.
9. Biochemical changes including C Reactive Protein (CRP), IL-6, albumin and pre-albumin from baseline.
10. Survival (overall and cancer-specific) measured with data of death from the time of enrolment.
11. Changes overtime in the participant rated Global Impression of Change (GIC) and in the clinician rated Clinical Global Impression of Severity and Improvement (CGI-S, CGI-i).
12. Changes overtime in quality of life measured by EQ-5D-5L (EuroQoL five-dimensional instrument) and ICECAP-A (ICEpop CAPability measure for Adults).

13. Changes overtime in participant-reported fatigue as measured by the Functional Assessment of Chronic Illness Therapy-Fatigue (FACIT-F) domain.
14. Rates of unplanned hospitalisations (defined as an emergency admission; or unplanned emergency contact with GP, nurses, specialists, home help visit, etc.; or unplanned readmission within 28 days following discharge to the same facility – participant may arrive at hospital in own transport or in an ambulance) and length of stay; with primary reasons kept in a diary by participants.
15. Episodes of febrile neutropaenia will be collected from participant's medical record.
16. Adverse events from chemotherapy (nausea, vomiting, anorexia, fatigue) will also be collected from participant's medical record.
17. Harms assessed in each visit.

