## 3.0 STUDY DESIGN, SETTING AND POPULATION

### 3.1 Study design

This is a multi-site, randomised, double-blind, placebo-controlled, parallel arm, fixed dose, phase II study.

A total of 50 participants with SCLC and anorexia will be randomised 1:1 to oral anamorelin HCl 100mg (Group 1 / intervention arm) or placebo (Group 2 / control arm) once daily ( $\geq 1$  hour before first meal of the day) for at least 12 weeks. Study treatment (Day 1) will start as soon as practicable; ideally prior to cycle 1 of chemotherapy and **no later** than one day prior to scheduled date of cycle 2 of planned chemotherapy. If chemotherapy is not planned, Day 1 should occur within three weeks of screening visit. . At the end of the 12 weeks, participants are invited to enrol in an extension phase where they will continue to receive blinded intervention medication for another 12 weeks. The optional extension (weeks 13-24) is entirely based on participant's preference.

All participants will receive standard physical activity and diet advice leaflets from the study nurse as part of a multi-modal intervention at baseline.

Participants will visit the study centre at baseline, weeks 4, 8 and 12 (plus 18 and 24 for those in the extension phase). During the visits, the study nurse will take the measures and assessments. Primary and secondary efficacy analysis will be conducted at 12 weeks. Additional exploratory efficacy and safety analyses will also be conducted at 24 weeks (for those who opt into the extension phase) in order to collect data over longer treatment duration.

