### **5.1.3 Efficacy (for clinical assessments)**

1. Change in the 5-item Anorexia Symptom Scale Domain from the 12-item Functional Assessment of Anorexia Cachexia Treatment (FAACT, anorexia/cachexia – A/CS) scale by arm from baseline to week 12.
2. Rates of *on time, on dose* completion of any administered chemotherapy and/or radiotherapy for SCLC during the duration of the study.

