## **6.2 Clinical and physical measurements**

**Height** in centimetres (cm) will be collected at screening (Visit 1). The patient's height will be recorded to the nearest 0.5 cm while the patient is barefoot and standing.

**Body weight** in kilograms (Kg) will be collected at every visit: screening visit (Visit 1) and baseline (Visit 2), Weeks 4, 8 and 12 (Visits 3, 4 and 5) as well as during optional extension phase at Weeks 18 and 24 (Visits 6 and 7). Clinical studies have shown that anamorelin administration resulted in an increase in body weight in patients with NSCLC and anorexia/cachexia hence, body weight will be recorded in this study in order to understand if a similar trend is observed for patients with SCLC and anorexia. In addition, historical stable weight will be gathered by self-reported weight (in Kg) in the last 1, 6 and 12 months collected at screening visit (Visit 1). A scale will be supplied to each participating site for consistency of data collected and to avoid miscalibrations.

**Body mass index** (BMI) will be calculated from the patient's weight divided by the patient's height squared.

**Body composition** will be obtained using dual x-ray absorptiometry (DEXA) and the lean body mass and fat mass will be recorded. In addition, bioelectrical impedance analysis (BIA), a simple, non-invasive, low-cost method will also be used to estimate body composition. These will be done at baseline (Visit 2) and at end of treatment, i.e. at Week 12 (Visit 5) (for those electing not to enter the extension phase) or Week 24 (Visit 7) for those participating in the extension phase, or at withdrawal, whichever occurs first. All measurements will be performed at a standardised time of day (morning or afternoon). Scales for BIA will be provided to each participating site for consistency. Furthermore, muscle segmentation in axial computed tomography (CT) images at the thoracic (T4) level will be obtained from all electronically stored data from CT scans whenever they are done clinically as part of usual care. Clinical studies have shown that anamorelin administration resulted in an increase in lean body mass in patients with NSCLC and anorexia/cachexia. Hence lean body mass will be assessed in this study in order to understand if a similar trend is observed for patients with SCLC and anorexia.

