### ***Participant acceptability of the study and proxy response measurement***

Participant's acceptability of the study is a primary endpoint under desirability. This will be assessed at the time of participant's last visit (Week 12 or Week 24 if the patient opts in to the study extension phase). A set of 3 questions will be asked to evaluate if participants find the study acceptable. In addition, information on whether

participant's required assistance to complete study tools will be evaluated by one screening question and two follow up questions if they answer 'No' to the screening question.

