b First telephone follow-up visit will occur 7 days after the Week 12 or Week 24 (if did not elect to enter extension) visit or the early termination visit due to withdrawal if treatment was ceased early. Subsequent telephone follow-up visits will occur every 7 days thereafter for a period of 4 weeks. There will be 4 follow-up visits in total.

Informed consent will be obtained prior to any study-related screening procedures.

ICECAP-A will be administered after the EQ-5D-5L questionnaire

\*Only if people elect NOT to enter the extension.

^ All electronically stored data from chest CT scans whenever they are done clinically will be used for evaluation of change in muscle mass at the thoracic (T4) level.

**Table 6-2** Schedule of Study Assessments for caregivers (Screening to Week 12 and optional extension – Weeks 13-24)

| Assessment                         | Patient screening | Baseline       | Visit Day Treatment Period |   |                 | Extension |                |
|------------------------------------|-------------------|----------------|----------------------------|---|-----------------|-----------|----------------|
| Week                               |                   |                | 4                          | 8 | 12              | 18        | 24             |
| Visit                              | 1                 | 2              | 3                          | 4 | 5               | 6         | 7              |
| Informed consent       | X                 | X ^ |                            |   |                 |           |                |
| EQ-5D-5L - quality of life         |                   | X              |                            |   | X* § |           | X § |
| Carer Experience Scale (CES)       |                   | X              |                            |   | X* § |           | X § |
| Diary (daily records by caregiver) |                   | X              | X                          | X | X               | X         | X              |

Informed consent will be obtained prior to any study-related procedures.

^OR (if consent not obtained during visit 1)

\*Only if patient elect not to enter the extension.

§ Or withdrawal

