## 10.0 STATISTICS

### 10.1 Power and sample size

A total of 50 participants with small cell lung cancer will be randomised 1:1 to anamorelin HCl 100 mg or placebo in order to have data at 12 weeks on 40 participants (approximately 20 in each treatment arm). Since this is a feasibility study, it is not required to calculate a fully justified sample size for establishing the efficacy of the intervention. It has been suggested, however, that in feasibility studies, a sample size between 24 and 50 is acceptable. The findings from this study will be used to inform the calculation of a sample size for a future larger scale phase III trial.

Participants discontinued after randomisation will not be replaced.

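### Follow-up DEXA, BIA and end-of-treatment IL-6 are taken at Week 12 only from people who decline the extension, so the planned 12-week comparison of lean body mass and IL-6 rests on a subset formed after randomisation

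*Supplement*

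**What the plan says.** The protocol fixes the time of analysis in section 3.1: "Primary and secondary efficacy analysis will be conducted at 12 weeks". The same section calls the 24-week analyses additional and exploratory, for those who opt in to the extension.

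Lean body mass is item 3 of section 5.2.1: "Change in lean body mass measured at baseline and week 12 (or 24) by dual x-ray absorptiometry (DEXA", with BIA as a second method. IL-6 is part of item 9.

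The schedule for these measures is the same wherever it appears:

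- Table 6-1 puts an asterisk on the Week 12 cells for DEXA, BIA and IL-6. The footnote reads "Only if people elect NOT to enter the extension".
- Section 6.2 places DEXA and BIA at baseline and at the end of treatment. That is Week 12 for those not continuing, and otherwise "Week 24 (Visit 7) for those participating in the extension phase, or at withdrawal, whichever occurs first".
- Section 6.1 places IL-6 at baseline, Week 4 and once at the end of treatment (Week 12, Week 24 or withdrawal).
- Section 7.5 lists BIA, DEXA and IL-6 at Visit 5 only in the branch for people who do not opt in. Section 7.7 lists them at Visit 7.

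Section 3.1 leaves entry to the extension wholly to the participant's preference at the end of the 12 weeks. Section 10.3 says that changes to 12 or 24 weeks will be calculated and compared between arms by t-test or Wilcoxon test, without imputation. It does not say which time point is used for whom.

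**The concern.** The stated analysis time and the measurement schedule do not fit together. Whether a participant has a Week 12 lean-mass value depends on a decision made after randomisation and after 12 weeks on blinded treatment. Perceived benefit, tolerability and fitness can all influence that decision, and treatment may affect each of them. The Week 12 groups are then no longer the randomised groups.

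Using each person's last value instead would compare changes over 12 weeks, over 24 weeks and up to a variable withdrawal date.

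The trial is meant to inform the size of a phase III study (section 10.1), and section 5.2.1 presents these endpoints as candidates for it. An effect estimate or standard deviation for lean mass taken from a selected subset would be a poor basis for that. A scan not done at Week 12 cannot be recovered later by analysis.

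**Working it through.** **Inputs from the documents.** Section 10.1: "A total of 50 participants with small cell lung cancer will be randomised 1:1", so that 40 have 12-week data, about 20 per arm. Extension uptake, the standard deviations and the size of any selection are not given. Values for them below are assumptions.

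**The plan's own figure.** The implied loss is 1 − 40/50 = 20%, and 40/(1 − 0.20) = 50. The figure reproduces. It can hold for Week 12 DEXA, BIA and end-of-treatment IL-6 only if nobody enters the extension.

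**Loss of precision.** With uptake *f*, equal in both arms, the number with a Week 12 value is 40 × (1 − *f*). The standard error grows by √(40/*n*), where *n* is that number.

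| Assumed uptake | With Week 12 value | Per arm | SE factor |
|---|---|---|---|
| 0% | 40 | 20 | 1.00 |
| 30% | 28 | 14 | √(40/28) = 1.20 |
| 50% | 20 | 10 | √(40/20) = 1.41 |
| 70% | 12 | 6 | √(40/12) = 1.83 |

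The 95% confidence interval half-width for a difference in means, in SD units, is t(0.975, 2m − 2) × √(2/m) with m per arm. At 20 per arm it is 0.64 SD. At 10 per arm it is 0.94 SD.

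**Selection, as an illustration.** Suppose the chance of opting in rises with lean-mass gain on a logit scale and about half opt in overall. With a slope of 1 per SD and a true difference of 0.5 SD, simulated uptake is 55% on active and 45% on placebo, and the difference among decliners is 0.41 SD. With a slope of 0.5 it is 0.47 SD. With no dependence it stays at 0.50 SD.

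**Mixing time points, as an illustration.** Suppose there is no drug effect and both arms change by −0.5 SD between Weeks 12 and 24. Pooling last values gives a spurious difference of −0.5 × (uptake on active − uptake on placebo). For 60% v 40% this is −0.10 SD. For 70% v 30% it is −0.20 SD. With equal uptake it is zero.

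**What is not affected.** Table 6-1 has FAACT, weight, CRP, FACIT-F, EQ-5D-5L, ICECAP-A and TUG at Week 12 for everyone. IL-6 is also taken at Week 4 in everyone, so one common on-treatment comparison remains for it.

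**The case against.** The strongest defence is one of proportion. This is a 50-person feasibility trial, and section 10.3 concentrates the primary analysis on feasibility thresholds and calls the between-arm tests exploratory. No threshold depends on DEXA, BIA or IL-6, and the FAACT efficacy endpoint is complete by design at Week 12. All of this stands, and it limits the weight of the point. It does not reconcile section 3.1 with the schedule.

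A second defence is that the uptake range is assumed and that the precision table takes uptake as equal across arms, whereas the bias illustrations need it to differ or to depend on outcome. That is also correct. The table therefore shows precision alone, and neither the direction nor the size of bias can be established from the documents.

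A reader might go further in four ways that the documents do not support:

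- **That the plan intends to pool 12- and 24-week values.** Sections 3.1 and 10.3 can be read as two separate analyses. Pooling is left open, not planned.
- **That AKPS and on-time, on-dose completion have the same fault.** The AKPS endpoint is "measured as area under the curve from data collected at every scheduled visit" and the completion endpoint is "for SCLC during the duration of the study". Both phrases leave the window unstated. However, AKPS and treatment adjustments are recorded to Week 12 in everyone, and section 8.12 carries study outcomes to 12 weeks for all. A common window already exists and only needs naming.
- **That acceptability loses its 12-week analysis.** Section 6.7 says "This will be assessed at the time of participant's last visit", and no 12-week change is planned. The times of asking differ, which is a limitation to note and no more.
- **That the caregiver scales break the 12-week rule.** They are tertiary and sit in Table 6-2, so section 3.1's statement on primary and secondary efficacy does not reach them.

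**Conclusion.** The point holds for DEXA and BIA, and in part for IL-6. As scheduled, a 12-week comparison of lean body mass between arms can use only people who chose not to continue. At assumed uptake of 30% to 70%, equal by arm, that is 28 to 12 people instead of 40, with a standard error 1.20 to 1.83 times as large. Selection bias of unknown size and direction would come on top.

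Severity is moderate. The endpoints are secondary and exploratory, and the primary feasibility analysis and the FAACT comparison do not depend on them. It is still worth correcting before measurements are taken, because the missing Week 12 values cannot be recovered.

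**What to change.** Take the follow-up DEXA, BIA and IL-6 at Visit 5 (Week 12) in all participants. For those entering the extension, move the DEXA from Week 24 to Week 12, so that no scan is added. BIA can stay at Week 24 as well for the exploratory analysis.

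Amend section 5.2.1 item 3, sections 6.1, 6.2, 7.5, 7.7 and 11.3.5, and Table 6-1. In section 10.3, state that the between-arm analysis uses Week 12 values and that Week 24 values are reported separately. The same sentence should say how values taken at withdrawal are handled.

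As minor clarifications, state that the AKPS area under the curve and on-time, on-dose completion use the common 12-week window. Note also that acceptability is asked at Week 12, Week 24 or withdrawal.

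The cost is small. Visit 5 already exists for everyone, section 6.2 supplies BIA scales to each site, and chemistry and CRP are already scheduled then. Section 6.1 lets routine clinical bloods stand in for some study samples, so sites would need to make sure that an IL-6 sample is actually drawn. The downside is that there would be no 24-week DEXA in the extension.

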### **5.2.2 Safety Assessments**

Safety assessments are made at all participant contacts, before efficacy assessments. The following safety assessments will be obtained during the study:

1. physical examination (PE);
2. vital signs;
3. 12-lead electrocardiogram (ECG);
4. laboratory tests (hematology and blood chemistry);
5. documentation of adverse events (harms);
6. overall survival on all participants; and
7. tumour assessments using CT scans whenever they are done clinically using RECIST (response evaluation criteria in solid tumours) criteria.

## **5.3 Tertiary endpoints**

### **5.3.1 Cost effectiveness and caregivers' assessments**

1. Changes in caregiver's quality of life measured by EQ-5D-5L and unmet needs measured by CES (Carer Experience Scale).

2. Capture participants and caregivers indirect and informal care costs and resource use (e.g. time off work, time spend in-home nursing or accompanying to hospital, any out-of-pocket expenses) kept in a diary by participants.

## 6.0 STUDY ASSESSMENTS

The study assessments are tabulated in Table 6-1. The study period will include 28 days after medication cessation (4 weekly follow-up period) or until death (whichever timeframe is shorter).

### 6.1 Laboratory measures

Venous blood samples (approximately 9mL/assessment) will be drawn for screening and follow up assessments. In some instances, blood samples taken as part of diagnosis and all pre-chemo/radiation therapy blood works can be used for screening, baseline and follow-up assessments if the clinical picture has not otherwise changed within that time. The results will be held in the participant study file as source data.

Samples for safety laboratory assessments will be taken at pre-set time points as specified in the Assessment Schedule and participant timeline. All tests require no fasting period for participants. All samples will be sent to the local hospital laboratory for analysis.

#### ***Haematology***

The haematology assessments will include full blood count (FBC) with differential count and will be performed at: screening visit (Visit 1), Week 4 (Visit 3) and Week 12 (Visit 5) as well as during optional extension phase of this study at Week 24 (Visit 7).

#### ***Blood Chemistry***

Blood Chemistry will include sodium, potassium, chloride, calcium, total protein, albumin and pre-albumin, aspartate aminotransferase [AST (SGOT)]\*, alanine transaminase [ALT (SGPT)]\*, alkaline phosphatase (ALP), total bilirubin, creatinine [creatinine clearance\* will be calculated using the modification of diet in renal disease (MDRD) formula (the current Australian national standard)], haemoglobin A1c (HbA1c) and random glucose\*\*. These will be performed at the screening visit (Visit 1), Week 4 (Visit 3) and Week 12 (Visit 5) as well as during the optional extension phase of this study at Week 24 (Visit 7).

In addition, blood samples for IL-6 will be collected at baseline (Visit 2), Week 4 (Visit 3) and at end of treatment (i.e. either Week 12 (Visit 5), Week 24 (Visit 7) or at Withdrawal).

C-reactive protein (CRP) will be collected at baseline (Visit 2), Week 4 (Visit 3), Week 12 (Visit 5) as well as during the optional extension phase of this study at Week 24 (Visit 7). C-reactive protein will be used to assess the level of infection or inflammation in the body.

\*Notes: Only patients with a calculated creatinine clearance of >20ml/min will be eligible to participate in the study. Similarly, liver function, as measured by AST (SGOP) and ALT (SGPT) will be assessed prior to entry into the study, with an expected result of  $\leq 5 \times \text{ULN}$  for eligibility.

\*\*Notes: All participants with diabetes enrolled in this study will be required to monitor their blood glucose levels in consultation with their treating physician. People who are insulin dependent will be encouraged to commence daily monitoring (if not already doing so) in consultation with their treating physician. During their participation in the study, blood glucose levels and HbA1c concentrations will be assessed as part of blood chemistry at specified study visits [including, screening visit (Visit 1), Week 4 (Visit 3), Week 12 (Visit 5) and at Week 24 (Visit 7, if applicable)]. Changes in blood glucose levels will be reviewed as adverse events.

### ***Pregnancy Screening***

Urine pregnancy testing for women of childbearing potential will be performed at screening visit (Visit 1), baseline (Visit 2) and Week 12 (Visit 5).

A negative urine pregnancy test will be needed at baseline prior to first dose of investigational product.

## **6.2 Clinical and physical measurements**

**Height** in centimetres (cm) will be collected at screening (Visit 1). The patient's height will be recorded to the nearest 0.5 cm while the patient is barefoot and standing.

**Body weight** in kilograms (Kg) will be collected at every visit: screening visit (Visit 1) and baseline (Visit 2), Weeks 4, 8 and 12 (Visits 3, 4 and 5) as well as during optional extension phase at Weeks 18 and 24 (Visits 6 and 7). Clinical studies have shown that anamorelin administration resulted in an increase in body weight in patients with NSCLC and anorexia/cachexia hence, body weight will be recorded in this study in order to understand if a similar trend is observed for patients with SCLC and anorexia. In addition, historical stable weight will be gathered by self-reported weight (in Kg) in the last 1, 6 and 12 months collected at screening visit (Visit 1). A scale will be supplied to each participating site for consistency of data collected and to avoid miscalibrations.

**Body mass index** (BMI) will be calculated from the patient's weight divided by the patient's height squared.

**Body composition** will be obtained using dual x-ray absorptiometry (DEXA) and the lean body mass and fat mass will be recorded. In addition, bioelectrical impedance analysis (BIA), a simple, non-invasive, low-cost method will also be used to estimate body composition. These will be done at baseline (Visit 2) and at end of treatment, i.e. at Week 12 (Visit 5) (for those electing not to enter the extension phase) or Week 24 (Visit 7) for those participating in the extension phase, or at withdrawal, whichever occurs first. All measurements will be performed at a standardised time of day (morning or afternoon). Scales for BIA will be provided to each participating site for consistency. Furthermore, muscle segmentation in axial computed tomography (CT) images at the thoracic (T4) level will be obtained from all electronically stored data from CT scans whenever they are done clinically as part of usual care. Clinical studies have shown that anamorelin administration resulted in an increase in lean body mass in patients with NSCLC and anorexia/cachexia. Hence lean body mass will be assessed in this study in order to understand if a similar trend is observed for patients with SCLC and anorexia.

A **complete physical examination** (PE) of the patient will be completed at the initial screening (Visit 1) to obtain a medical assessment of the patient's general condition and at follow up visits (Visits 3, 4, 5 and 6 and 7, if applicable). This evaluation will include an examination of general appearance, head, eyes, ears, nose, throat, skin, neck, lungs, cardiovascular, breast, lymph nodes, abdomen, musculoskeletal and neurological. The medical examination will also include a complete cardiac history to assess for previous or recent cardiac events, and will make use of physical examination, close review of the medical record, and assessment of the New York Heart Association Classification, if appropriate.

In addition, a **dedicated physical exam** aiming to monitor signs and symptoms of **oedema** such as pedal oedema, pericardial effusion, pleural effusions, and ascites will be conducted at screening (Visit 1) and follow up visits (Visits 3, 4, 5 and 6 and 7, if applicable). Limb oedema (tibia, feet including ankles, and hands) should be evaluated for pitting (and graded 0-4+), and whenever possible, for tenderness to palpation (by applying pressure), skin temperature, colour, and texture changes. This will be done since excess in body water may contribute to a change in body weight and confound the primary efficacy analysis. PE of limbs should focus on the dorsum of the foot, all foot including ankle, the medial malleolus, the bony portion of the tibia. PE of ascites, pleural and pericardial effusions should focus on visual and palpation assessment of the abdominal area and evaluation of thoracic/pericardial oedema will be complemented by auscultation.

Information about the physical examinations will be recorded in the source documentation at the site and any abnormalities at screening will be recorded in the eCRF. After signing the informed consent, development or worsening of existing pathological findings noted since previous examination during the study will be reported on the AE eCRF form.

**Vital signs** including body temperature (°C), blood pressure (mmHG, systolic and diastolic), respiratory rate (breaths per minute) and heart rate (beats per minute) will be measured as part of the safety assessments at every visit: screening (Visit 1) and at Weeks 4, 8 and 12 (Visits 3, 4 and 5) as well as during optional extension phase at Weeks 18 and 24 (Visits 6 and 7). Pulse rate, systolic and diastolic blood pressure will be measured after the patient has been resting in the semi-supine position for at least 5 minutes.

A **complete medical history** will be recorded at the screening visit (Visit 1) and will include evaluations for past or present conditions. **Concomitant medications** will also be recorded at every visit: screening (Visit 1), baseline (Visit 2) and at Weeks 4, 8 and 12 (Visits 3, 4 and 5) as well as during optional extension phase at Weeks 18 and 24 (Visits 6 and 7).

**12-lead ECGs** will be conducted at screening (Visit1), Weeks 4, 8 and 12 (Visits 3, 4 and 5). Any new or worsening ECG abnormalities assessed to be clinically significant by the study investigator will be reported as adverse events. When possible, ECG will be recorded at 1 hour ( $\pm 5$  minutes) post dose to align with occurrence of Cmax. At screening visit ECG will be taken pre-dose (as no dose will be administered at this time).

**Short Blessed Test** will be administered at screening to assess cognitive capacity and will assist the PI to assess eligibility by determining the persons capacity to understand the study and to complete the assessments. A score of 10 or more is required.

**Adverse event assessment** the research team member who sees the participants and their caregivers will also ask about any other unexpected adverse outcomes. The study investigators will oversee the research team members. All serious adverse events will be reported in accordance with the requirements of the approving central Research and Ethics Committee as defined in the committee's safety reporting standard operating procedures (see section 9.1 Adverse Events). Serious adverse events will be followed until documentation of resolution or the successful initiation of relevant management strategies. Other adverse events will be described in the Annual Report to the Committee.

